## Introduction

Globally, adolescents and young adults between 14–29 years represent 30% of HIV incidence cases among persons of reproductive age, with the vast majority of cases (~75%) occurring in sub–Saharan Africa (SSA) [1]. HIV incidence rises rapidly in SSA, as adolescents and young adults leave school (often prematurely) and migrate for work and marriage [2–4]. In particular, older adolescents are more likely to experience increased experimentation with health-compromising behaviors that increase their vulnerability to HIV and sexually transmitted infections (STIs), including sexual risk behaviors and alcohol/ drug misuse [5–7]. Young people orphaned by AIDS (YPoAIDS), 80% (~10 million) of which live in SSA represent a particularly vulnerable and unique population [8]. Between 2012–2018, our *Bridges to the Future* study team prospectively followed 1,383 adolescents (10–16 years at study enrollment, who lost one or both parents to AIDS), across 48 primary schools in Uganda, to evaluate the efficacy and cost-effectiveness of a family-based economic empowerment intervention (EEI) comprising of child development accounts, financial literacy training, family income generating activities and peer mentorship. Our findings show short-term success with reduction in multidimension poverty incidence (*b*−0.107, SE = 0.034, p<0.001) [9], improving self-related health (B = 0.25, 95% CI = 0.06–0.43) and emotional well-being, including lowered depression (B = -0.28, 95% CI = -0.43–0.125), hopelessness (B = 0.05, 95% CI = –0.11, 0.21), improved self-concept (B = 0.26, 95% CI 0.09–0.44), and adherence self-efficacy (B = 0.26, 95% CI = 0.09–0.43); reduced self-reported sexual risk-taking behaviors (B = 0.05, 95% CI = –0.11, 0.21) [10,11]; and positive educational outcomes among intervention participants, including better academic performance (*b* = −3.78, 95% CI = −4.92, −2.64, *p* ≤ 0.001) and higher odds of transitioning to post primary education (OR = 1.66, 95% CI = 1.28, 2.18, *p* ≤ 0.001) [9–12]. However, critical questions related to the longitudinal impact of economic empowerment on HIV prevention and engagement in care among YPoAIDS remain.

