#### Overview of the *Original Bridges* study (2012–2018)

The overall goal of *the Original Bridges* study was to evaluate the efficacy and cost-effectiveness of the *Bridges* intervention (detailed below) for YPoAIDS. The study recruited 1383 school-going adolescents (average age 12.7 years). Participants were included if they met the following inclusion criteria: 1) an AIDS-orphaned child/adolescent, defined as one who had lost one or both parents to HIV/AIDS; 2) enrolled in school; 3) in the last two years of primary school; 4) between ages 10 to 16 years; and 5) living within a family (broadly defined and not an institution; institutions have different familial needs). Participants were ineligible if they were not able to comprehend the study procedures as assessed during the informed consent process. Participants were recruited from 48 primary schools in the greater Masaka Region of Uganda (Masaka, Rakai, Kyotera, Lwengo and Kalungu, five districts hardest hit by HIV/AIDS—prevalence 11.7% vs. 5.4% national average) [69]. Using a cluster-randomized controlled trial (RCT), 48 primary schools were randomly assigned to three study arms (n = 16 schools in each arm): 1) control arm receiving usual care, 2) the *Bridges* arm receiving a Child Development Account (CDA—see description in Fig 1) with a 1:1 match, financial education, and mentorship), and the *Bridges PLUS* arm receiving a CDA with a 2:1 match, financial education, and mentorship. The only difference between the two treatment arms was the match rate: 1:1 vs. 1:2. The match rate was specifically varied to address the incentivizing and cost-effectiveness question. As indicated in Fig 1 below, both *Bridges* and *Bridges PLUS* included the following intervention components that had been tested in two earlier studies [31–37].

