**Demographics**		
Socio-demographics: Age; sex (assigned at birth), orphanhood status; socioeconomic status; family composition		**T1-RC, 12, 24

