#### Time points used in proposed inferential analyses

To maximize the rigor of the analyses; to assure alignment of biomarker data (only measured in the *Bridges-R2*) and our remaining outcomes; and to avoid reuse of *Original Bridges* study outcomes (already examined for shorter-term intervention efficacy) and biased examination of longer-term intervention efficacy, all proposed primary inferential analyses and most of the proposed secondary inferential analyses listed will use only *Bridges-R2* data. The exception is longitudinal developmental trajectory analyses proposed to explore associations between changes in time-varying covariates and mechanisms of change with outcomes measured across both studies.

#### Primary analyses for Aim 1

We hypothesize that: H1a. Relative to the control group, participants in the *Bridges* intervention group (1:1 savings incentive match rate) will have a lower odds of HIV infection at the final measurement point; H1b. Relative to the control group, participants in the *Bridges PLUS* intervention group (1:2 savings incentive match rate) will have a lower odds of HIV infection at the final measurement point; and H1c. Relative to the *Bridges* intervention group, participants in the *Bridges* PLUS intervention group will have a lower odds of HIV infection at the final measurement point. To test H1a-H1c, we will fit a two-level generalized linear mixed model (GLMM) with fixed effects for study arm, time, and their interaction. We will use random intercepts for school ID to account for clustering of persons within schools. Reflecting the binary HIV status outcome, a binomial distribution and logit link will be used. To test H1a-H1c we will perform three pairwise planned comparisons. Alpha (α) will be set at .05/3 = .017 for these three comparisons to maintain a nominal α = .05. We will adjust for orphanhood status, the only covariate where imbalance was detected in our *Original Bridges* data. It is important to note that previously, deaths have been very few; however, if numbers of deaths become non- trivial, we will extend our proposed GLMMs to jointly model survival and the odds of HIV infection simultaneously [115].

#### Secondary exploratory analyses for Aim 1

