#### Sex as a biological variable

All previously described analyses will be repeated with models extended to include sex assigned at birth as a moderator to examine whether effects vary by participant sex. For male participants, we will perform additional exploratory analyses at each time point using a three-level GLMM to explore whether medical male circumcision differs by intervention group.

#### Qualitative data analysis for Aim 3

All interviews will be transcribed and translated from Luganda into English. Transcripts will be compared with digital records to ensure transcription accuracy. All transcripts will be uploaded to QSR NVivo12 analytic software for data analysis. Interview transcripts will be reviewed by the research team to develop a broad understanding of content as it relates to the project’s specific aim and to identify topics of discussion and observation. During this step, as well as during subsequent steps, analytic memos will be written to further develop categories, themes, and subthemes, and to integrate the ideas that emerge from the data [124]. Using analytic induction techniques [125], transcripts will be read multiple times for initial coding by the research team. For initial coding, randomly selected 10 interview transcripts will be read multiple times and independently coded by the project investigators using a priori (i.e., from the interview guide) or emergent themes (also known as open coding) [124]. Broader themes/ categories will be broken down into smaller, more specific units until no further subcategory is necessary. Qualitative findings will also shed light into potential mediators and moderators for sexual risk-taking and mental health.

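### The primary Aim 1 model takes its only covariate from an imbalance check and omits age and sex, giving up a modest gain in power and some protection against uneven loss

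*Protocol article*

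**What the plan says.** In the protocol article, Primary analyses for Aim 1 specifies a "two-level generalized linear mixed model (GLMM) with fixed effects for study arm, time, and their interaction", with random intercepts for school, a binomial distribution and a logit link. One covariate is added, with its reason: "We will adjust for orphanhood status, the only covariate where imbalance was detected in our" Original Bridges data. Age and sex do not appear in this model.

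Both are collected. The demographics row of Table 2 lists "Socio-demographics: Age; sex (assigned at birth), orphanhood status; socioeconomic status; family composition" at re-consent, 12 and 24 months.

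Sex is used elsewhere. Under Sex as a biological variable, "All previously described analyses will be repeated with models extended to include sex assigned at birth as a moderator". That is a set of repeat analyses, separate from the three confirmatory comparisons.

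On age, the Overview of the Original Bridges study gives eligibility "between ages 10 to 16 years", with a mean of 12.7 years. The Introduction says "HIV incidence rises rapidly in SSA, as adolescents and young adults leave school", and adds that older adolescents experiment more with behaviours that raise HIV vulnerability.

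On incomplete data, the missing-data section plans direct maximum likelihood and multiple imputation under MAR, with auxiliary variables that it does not name, and pattern-based imputation as a sensitivity analysis.

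**The concern.** A covariate earns its place in a randomised comparison by predicting the outcome. A detected imbalance is a weak criterion. It picks up chance differences whether or not they matter for HIV, and passes over strong predictors that happened to be balanced.

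The check was also made on a different set of people. It describes the Original Bridges sample of 1383, whereas the Statistical power analysis section allows for as few as 799 at the final wave. Loss between the two could change the balance of any variable.

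Two things are at stake. The first is power: a logistic model that omits predictors of the outcome tests the arm effect less efficiently than one that includes them. The second is robustness: if the people lost differ in age or sex in one way in one arm and another way in another, the model has nothing to correct the resulting difference.

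**Working it through.** **1. Reproduce the plan's own figure.** Inputs from Statistical power analysis: final N 799, control prevalence 19.7%, ICC .12, alpha .017, power .80. From the Original Bridges overview: 48 schools, 16 per arm. Two-sided testing is assumed, since sidedness is not stated.

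- Mean cluster size: 799/48 = 16.65.
- Design effect: 1 + (16.65 − 1) × .12 = 2.877 (unrounded cluster size).
- Effective n per arm: 16 × 16.65 / 2.877 = 92.6.
- At 19.7% v 4.4% (difference 15.3 points, mean .1205), the null SE is √(2 × .1205 × .8795 / 92.6) = .0478. The alternative SE is √((.197 × .803 + .044 × .956) / 92.6) = .0465.
- Power: Φ((.153 − 2.387 × .0478) / .0465) = 79.8%, against the stated 80%.
- Solving for 80% power gives 15.33 points, against the stated 15.3. A t-based calculation with 30 df gives h = .4985, against the stated .499.

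The power statement stands and does not depend on covariate adjustment.

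**2. How much of the sample the imbalance check describes.** 799/1383 = 57.8%. At worst, about 42% of those in whom balance was assessed are not in the final analysis.

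**3. Efficiency from adding age and sex.** The documents give no odds ratios for either, so these are assumptions: sex 1.5 to 3, age 1.2 to 2 per SD. Expected information matrices were computed for the logistic model with arm alone and with arm, sex and age. Relative efficiency is the ratio of squared z statistics, (adjusted log-OR² / adjusted variance) ÷ (unadjusted log-OR² / unadjusted variance). Clustering was ignored in this step.

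- Across the grid, at 19.7% v 4.4% and at 19.7% v 10%, the gain is about 1% to 10%. The upper end arises at the smaller treatment difference.
- The gain does not come from a smaller standard error. At 19.7% v 4.4% the unadjusted log-OR is ln(.044/.956) − ln(.197/.803) = −1.67. The conditional log-OR lies between about −1.7 and −1.8, and its variance rises slightly. The estimate moves further from zero than its standard error grows.
- Multiplying the effective n of 92.6 by 1.01 and by 1.10 takes power at 15.3 points from 79.8% to 80.2% and 84.0%. The detectable difference goes from 15.3 to 15.3 and 14.8 points. The 1.10 end is an outer bound for a difference this large.

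**4. When omission causes bias.** A large two-arm simulation with no treatment effect used assumed odds ratios of 2 for sex and 1.5 per SD of age, with about 65% retained.

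| Loss depends on age and sex | Unadjusted OR | Adjusted OR |
|---|---|---|
| Equally in both arms | 1.00 | 1.00 |
| Differently by arm | 1.14 | 1.00 |

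In the second row the retention slopes for age and sex were −0.5 on the logit scale in one arm and +0.2 in the other. This pattern was imposed to show the mechanism and is not an estimate for this cohort.

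**The case against.** The plan is not careless here. Schools were randomised, so leaving out a predictor does not bias the arm contrast. Sex is modelled, if only in repeat analyses. The missing-data section brings in auxiliary variables, which can carry age and sex into the imputation without their being in the analysis model, and tests MAR with pattern-based imputation. An article may leave the naming of auxiliaries to a fuller document. All of this stands, and it limits the size of the point.

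The age spread is also less certain than the eligibility range suggests: entry was restricted to the last two primary years and no SD is reported.

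A reader might infer more than the documents support:

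- **That age and sex drive loss to follow-up.** No section relates either to attrition. The Introduction supports age as a correlate of HIV vulnerability, in general terms, and nothing says that sex drives HIV risk in this cohort.
- **That uneven loss by age or sex necessarily distorts the result.** It does so only if the dependence differs by arm, as step 4 shows.
- **That the precision lost is large.** Scaling variance components as in a linear model (.12 + .88/16.65 = .173) gives a 1.5% to 3.1% reduction if 5% to 10% of within-school variance is explained. It reaches 10% to 17% only by also assuming that 10% to 20% of between-school variance is explained. Nothing in the documents supports that, and the calculation does not carry over to a logit mixed model.

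What the objection leaves standing is that the article does state the confirmatory covariate set and its reason, and the reason is a poor one. A moderator repeat does not adjust the primary test, and unnamed auxiliaries do not show that age and sex are covered.

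**Conclusion.** The point holds as a modest weakness in a stated analysis choice. The primary model's one covariate was picked by an imbalance check in a sample of which as little as 57.8% may be analysed, while age and sex, already collected, are left out of the confirmatory test.

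Under the assumed odds ratios the cost is about 1% to 10% in efficiency, or at most about half a point on the detectable difference. The contrast is also less protected against arm-differential loss by age or sex. The documents neither show such loss nor clearly guard against it.

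It would be wrong to conclude that the planned comparison is biased or that the power statement is in error.

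**What to change.** In Primary analyses for Aim 1, replace the imbalance-based sentence with a prespecified set: age at Original Bridges enrolment, sex assigned at birth, and orphanhood status as recorded at the Original Bridges baseline. Naming the baseline value settles which orphanhood measurement is meant, since Table 2 records it again at each Bridges-R2 wave. Because the plan restricts primary analyses to Bridges-R2 data, add that this restriction concerns outcomes and does not exclude these baseline covariates.

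Name the same three variables as auxiliaries in the missing-data models.

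Label the resulting odds ratio as conditional on these covariates, since it will generally lie further from 1 than the unadjusted one.

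No new data collection is needed. The cost is a few sentences of plan wording, provided the change is made before outcomes are compared by arm.

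### The primary HIV model takes its only adjustment covariate from a balance check on the original sample and leaves out enrolment age and sex, forgoing a modest gain that costs almost nothing.

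*Protocol article*

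**What the plan says.** Under Primary analyses for Aim 1, the protocol article describes a two-level GLMM "with fixed effects for study arm, time, and their interaction". On clustering it says: "We will use random intercepts for school ID to account for clustering of persons within schools". For the outcome, "a binomial distribution and logit link will be used". The one covariate and the reason for it follow: "We will adjust for orphanhood status, the only covariate where imbalance was detected in our" Original Bridges data.

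Enrolment age and sex do not appear in that model. Both are available. Age 10 to 16 was an eligibility criterion of the original trial, and the Demographics rows of Table 2 list "Age; sex (assigned at birth), orphanhood status; socioeconomic status; family composition" at all three Bridges-R2 waves. Sex enters the analysis only under Sex as a biological variable, where analyses are repeated with "models extended to include sex assigned at birth as a moderator". The original schools lay in "five districts hardest hit by HIV/AIDS"; the article states neither stratification of the randomisation by district nor separate HIV figures for the districts.

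**The concern.** The article names the covariate and gives its rationale, so this is a stated choice and not a detail left to an analysis plan. The rationale is weak for three reasons.

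- **Imbalance is the wrong criterion.** In a randomised comparison, a detected baseline imbalance is a chance event and says nothing about whether the variable predicts HIV. Covariates earn their place by being prognostic and fixed before randomisation.
- **The check was made on a different set of people.** It concerned the Original Bridges data (1383 enrolled). The primary comparison is at the final wave, where the plan counts on 799, or 58%. Balance at enrolment need not survive that loss.
- **The article's own reasoning points to other variables.** The Introduction and the section on emerging adulthood describe HIV risk rising as young people leave school and become sexually active. Participants enrolled at 10 to 16 sit at different points on that rise at any given wave. Sex is thought important enough for every analysis to be repeated with it as a moderator.

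There is also a loose end. Table 2 remeasures orphanhood at each Bridges-R2 wave, and the primary analyses are said to use only Bridges-R2 data, so it is unclear which orphanhood value is meant. A value recorded after randomisation is a poorer choice than the enrolment value.

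At stake are a little power, and protection of the arm comparison against differences in age and sex mix.

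**Working it through.** **Inputs from the Statistical power analysis section and the overview of the original trial:** control prevalence 19.7%, ICC .12, alpha .017 (taken as two-sided), power .80, final N 799, 48 schools, 16 per arm. Hence 799/3 = 266.3 per arm and 799/48 = 16.65 per school.

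**1. Reproduce the plan's figure.** Design effect = 1 + (16.65 − 1) × .12 = 2.878. Effective n per arm = 266.3/2.878 = 92.6. The pooled two-proportion formula gives a minimum detectable difference of 15.33 points (h = .498), against the stated 15.3 (h = .499). Power at exactly 15.3 points is .798.

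**2. Assumed prognostic strength.** The article gives none, so a range is used: women-to-men odds ratio 2 to 3, odds ratio 1.2 to 1.3 per year of age, half the sample female, age SD 1.3 years.
- Sex: R² = ((pF − pM)/2)² / (p(1 − p)). At OR 2 the prevalences are 25.1% and 14.3%, R² = .018. At OR 3 they are 27.9% and 11.5%, R² = .043.
- Age: R² ≈ p(1 − p) × (ln OR)² × SD². At 1.2 per year .009; at 1.3 per year .018.
- Sum: about .03 at the low end and .06 at the high end.

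**3. Gain at the plan's ICC.** Individual-level covariates act on the within-school part only, so the design effect becomes (1 − ICC)(1 − R²) + 16.65 × ICC.

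| R² within schools | Design effect | Effective n per arm | Gain | Power at 15.3 points | Detectable difference |
|---|---|---|---|---|---|
| 0 | 2.878 | 92.6 | – | .798 | 15.33 |
| .03 | 2.851 | 93.4 | 0.9% | .802 | 15.27 |
| .06 | 2.825 | 94.3 | 1.9% | .806 | 15.22 |

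The gain is small because, at ICC .12, the between-school part is 16.65 × .12 / 2.878 = 69% of the variance.

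**4. Lower ICC.** The .12 comes from earlier Bridges data, whereas biomarkers are measured only in Bridges-R2, so it cannot be an ICC for assayed HIV status. With the same R² range, the effective-sample gain is 1.3% to 2.7% at ICC .07 and 2.3% to 4.7% at ICC .02.

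**5. Simulation check.** The set-up was 48 schools of 17, school SD .94 on the logit scale (observed-scale ICC .12), a school-level t-test, a true difference of 10 points and 4000 runs per scenario. Adding sex and age moved power from .417 to .419 (OR 2; 1.2 per year) and from .413 to .418 (OR 3; 1.3 per year). This simulation assumed that age and sex mix do not differ systematically between schools.

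**6. Chance differences in mix.** With about 266 per arm and half female, the SD of the difference in female share between two arms is √(2 × .25/266) = 4.3 points (95% range about ±8.5), before any clustering of sex by school. At OR 3 the sex gap in prevalence is 16.5 points, so an 8.5-point difference shifts the crude contrast by 1.4 points, and a 10-point difference by 1.65.

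**7. District.** Four indicators use 4 of the 45 school-level degrees of freedom. In the same simulation, power without and with district was:

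| Assumed share of between-school variance due to district | Without district | With district |
|---|---|---|
| 0% | .417 | .375 |
| 10% | .418 | .399 |
| 28% | .441 | .452 |
| 55% | .468 | .542 |

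The sign depends on a share that the article does not give.

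**The case against.** The strongest reply is that one prespecified covariate gives a valid test, so this is a preference about efficiency and not an error. That stands as far as validity goes. Three further points deserve weight.

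- **Part is already covered.** The HIV model will be rerun with sex in it, and auxiliary variables are used when handling missing data. But the rerun is a moderation analysis and not the primary test, and auxiliary variables do not put age or sex into the arm comparison.
- **No imbalance in age or sex is reported.** Orphanhood was the only covariate flagged. The standard error already allows for chance imbalance, and a shift of about 1.5 points is small beside a detectable difference of 15.3. This is fair, but the article does not say which variables were checked, and the check predates the loss from 1383 to about 799.
- **Adjustment changes the estimand.** With a logit link, adding prognostic covariates does not shrink the standard error of the log odds ratio. It moves the target to a more conditional odds ratio, and power can rise because the estimate moves away from the null. This is a real consequence and should be stated in the plan.

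A reader might go further and infer that substantial precision is being thrown away, or that adding age, sex and district would raise power at no cost. The documents support neither. They give no prognostic strength for any of these variables, the calculable gain for age and sex is small at ICC .12, and district can lower power. Since no stratification by district is stated, leaving it out breaks no match between design and analysis.

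**Conclusion.** The point holds in a limited form. The rule for choosing the covariate is unsound, and two pre-randomisation variables that the article itself links to HIV risk or to a varying effect are missing from the primary model.

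The size is modest: about 1% to 2% more effective sample and up to about 1 power point at ICC .12, rising to about 2% to 5% more effective sample if the ICC for HIV were near .02. There is also some protection against differences in age and sex mix from chance or attrition. These figures rest on assumed odds ratios, an assumed even sex split and an assumed age SD; none is in the article. The primary test is not invalid without the change.

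**What to change.** In Primary analyses for Aim 1, replace the sentence on orphanhood. State that the H1a–H1c GLMM includes, as fixed effects, age at original enrolment, sex assigned at birth and orphanhood status at original enrolment, chosen in advance as prognostic pre-randomisation variables. Delete the reference to detected imbalance. Add that the reported odds ratios are conditional on these covariates as well as on the school effect.

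Do not require district in the primary model; at most, report a sensitivity analysis that includes it.

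The cost is two extra fixed effects if age is entered linearly, no new data and a sentence or two of text. The one real consequence is the more conditional interpretation of the odds ratio.
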